## Pre-clinical and clinical data

### Pre-clinical data

ETI crosses the placenta and is detectable in breast milk, so will be encountered by the fetus in utero during critical organogenesis and by the infant early in postnatal development. Despite the small sample size in the Collins et al study (7) evidence of placental transfer of ETI suggests that the already established risks of ETI-administration in children such as hepatotoxicity, cataracts and hypertension should be considered.

Ivacaftor, a component of ETI, was first linked to cataracts in a pre-clinical study in juvenile rats (11). Rat pups which were dosed from postnatal days 7 – 35 developed cataracts at doses as low as 0.1X the maximum recommended human doses. However, a more recent animal study (12) which investigated CF-ferrets exposed to ivacaftor both in utero and throughout adulthood, did not show any lens abnormalities.

A 2024 study (13) investigated the tissue distribution pattern in rat fetuses exposed to maternally administered ETI. Fetal rats were exposed to seven days of maternally ingested oral treatment from day 12 to 19 of embryonic life. The fetal tissue sample was dissected at embryonic day 19 with analysis calculating an average entry ratio (based on tissue/plasma concentration) exceeding 100% in all tissues indicating accumulation of the drug. This was most significant in the liver at 200%, but levels in the lung, muscle, and small intestine were also approximately 100%.

In the same study Li et al. (13) also reported measurable ETI-accumulation in the embryonic rat-brain tissue at approximately 50% maternal rat-serum concentration, and although lower than other tissues, this confirms the ability of CFTRm components to cross the blood-brain barrier in this CF-animal model. Brain/plasma ratios in adult rats were significantly lower compared to the rat-pups suggesting the blood brain barrier’s greater ability to limit transfer reserved for older groups. In a recent case series (14) this possibility was raised when three children with CF developed raised intracranial pressure while on ETI, although causation could not be inferred and shifts in fat soluble vitamins could also be implicated.

The effect on the developing lung has also been raised. Although from a non-human in vitro model system, Hullier et al (15) reported that ETI, applied during the pseudo glandular stage of murine lung development, adversely affected lung branching and led to the formation of abnormal bronchial terminal dilatations. Data of this nature have not been replicated in in vivo animal or human studies.

### Clinical data

Existing studies of females with CF showed a degree of subfertility (15) when compared to the general population, thought to be multifactorial. Those females with CF who did get pregnant were found overall to have an increased rate of premature birth, lower birth weight infants, and higher risk of obstetric complications such as gestational diabetes (16). Significant bacterial pathogens were also implicated in the poorer longer-term outcomes, with a case series showing that three out of four women who died shortly following pregnancy were chronically infected with *Burkholderia cenocepacia* (18).

More recent studies have also looked at the implications of continuing/ceasing CFTRm in pregnancy. This has shown that those women who do stop will often restart due to significant deterioration in their own physical health (19)(5). Further studies have also shown that whilst the ante-partum period does not confer significant health risks, the first year of parenthood has resulted in increased risk of pulmonary exacerbations and overall health decline (20).

Whilst there are no known definitive side effects of CFTRm in infants exposed in utero, it is already recommended that those children with CF who are treated with ivacaftor or an ivacaftor containing compound should have yearly ophthalmology screening in case of cataract formation (11). It is unknown if in utero or lactation exposure to infants is equivalent to these directly administered therapeutic doses but raises questions already being explored.

Jain et al. (21) reported a case series in which 3 of 23 human infants born to mothers with CF taking ETI during pregnancy were diagnosed with bilateral congenital cataracts. The infants did not have any alternative explanation or risk factors for cataract formation. However, these cataracts were small, considered visually insignificant and were detected not on routine newborn eye checks using the red reflex, but at specialist paediatric ophthalmoscopy screening. The frequency of such subclinical changes in the general population is unknown. The current median prevalence of childhood cataract in the general population is 1 per 10,000 (22) with the sample size currently too small to make a comparison in an ETI exposed group.

A 2023 retrospective study(25) compared IRT levels between different groups of infants born in Indiana between 2020 - 2022. This included infants with IRT measurements below the cut-off levels for further testing, those diagnosed with CF, CF-carriers, and ETI-exposed infants (of which none were known to have CF). 191,493 infants were included, with 51 having CF, 489 carriers of a CFTR mutation, and 19 ETI-exposed. CF carriers not exposed to ETI had a mean IRT of 66.9 ng/ml while ETI exposed carriers had a statistically significant lower mean of 21.6 ng/ml (p <0.001). The mean for those with CF was 191.6ng/ml. Interestingly, the mean for those with an IRT below the threshold for testing, likely mainly non-carriers, was 25.4 ng/ml which was not significantly different to the ETI-exposed group (p=0.41). These findings suggest significantly lower levels of IRT in those exposed to ETI risking false negative results.

## Study Rationale and risk/benefit analysis

### Study Rationale:

There has been an increase in pregnancy rates in females with CF since the availability of CFTRm, and ETI in particular. This has created an opportunity for research into the experiences and management of females with CF during and immediately following pregnancy, in order to update guidelines and improve CF specific antenatal and postnatal management. This also extends to a better understanding of the impact on the females with CF of breastfeeding, something which has greater implications in CF due to its high metabolic demand. It is also important to use this opportunity to better understand how CFTRm, in particular ETI, impact the health of females with CF during pregnancy and how it may influence obstetric and neonatal outcomes.

This increase in pregnancy rates has directly resulted in an increase in infants exposed to CFTRm in utero or *via* breast milk. There is currently limited data on the health and developmental outcomes of these offspring. This includes the possibility of CFTRm exposure resulting in false negative CF-screening tests. This study aims to provide high quality data to support the creation of evidence-based guidelines on how best to manage this cohort of infants in the short and medium term.

The prioritisation of the need for this research is strongly endorsed by the receipt of a highly competitive CF Trust funded Strategic Research Centre grant following an international specialist peer-review process.

### Risks:

- Minimal pain associated with heel/finger prick blood tests/adult venepuncture.
- Sweat chloride tests can cause a tingling sensation on the skin but should be painless. On rare occasions a small burn can be caused.
- Lung MRI is a safe and painless investigation which does not involve any radiation. However:
  - it may scare some children due to loud noises or the tight spaces and the need to remain still.
  - it could be uncomfortable in later stages of pregnancy due to a need to lie supine.
  - it is also important to ensure that participants have no metal implants unsuitable for MRI.
- CT scans (‘Mama’ sub-study only) carry an additional risk of radiation. Some of the total radiation dose required by the study may be additional to routine clinical care for some participants. The risk of developing cancer as a consequence of taking part in this study is estimated as 0.03%.
- Qualitative interviews have the potential to cause distress, particularly around the recollection of traumatic or emotional events.
- Incidental findings of unclear significance discovered on investigations.
- Inconvenience of travel and visit burden to attend visits.
- Risk of communicable infections from attending visits in a hospital (see section 4.4)

### Benefits:

- Increased surveillance of possible CFTRm related sequalae allowing for appropriate management to be implemented if required.
- Contributing to data to support clinical guidelines on how best to manage and monitor infants exposed to CFTRm in utero or via lactation.
- Contributing to data to support how best to manage future pregnancies in females with CF.
- Increase understanding of the health impact of pregnancy and parenthood on females with CF to improve pre-conception counselling and post-pregnancy management and service delivery.

## Management of potential study risks

- Investigations carried out by qualified and trained health professionals.
- Public and patient involvement in design of study.
- Study based in a centre experienced in research.
- Infection control measures to avoid any cross infections with other patients. This will include the use of a private room for all visits and following local SOP for cross-infection control in CF outpatient clinic settings.
- Aligning maternal visits with standard care clinic visits to reduce study burden.
- Aligning infant visits with the timing of maternal visits.
- Working closely with parents to ensure comfort of the infant – for instance allowing breast feeding during heel prick blood test.
- Interviews are generally very low risk, although they often invite participants to explore sensitive or emotive topics (26). We will make it clear to participants that they can decline to answer specific questions or end the interview should they choose to do so. If it is clear to the interviewer that a participant finds particular questions or themes distressing, we will remind them that they can stop at any time. All participants will be provided with contact details of their clinical care team in case they have questions or would like to explore issues further after the interview. If the interviewer or analyser has concerns about a participant based on the content of the interviews, appropriate referral pathways will be followed.
- Incidental findings will be discussed with the appropriate clinician to provide context and a management plan.

# Study Aims and Objectives

## Primary aims

1. **Sub-study ‘Mama’**: To describe the impact of pregnancy and the first 12-24 months of parenthood in females with cystic fibrosis on their physical and psychological health.
2. **Sub-study ‘Mini’ & ‘Midi’:** To collect clinical data that will enable assessment of health outcomes in offspring of parents with CF in the short (up to 24 months) and medium-term (aged three-to-six years)

## Primary Objectives

1. **Sub-study ‘Mama’**
   1. To record the obstetric and neonatal outcomes of females with CF.
   2. To record CF-related health outcomes among females with CF including pulmonary (e.g. ppFEV_1_) and nutritional status (e.g. BMI) during pregnancy and early parenthood (up to 24 months).
   3. To record the subjective experiences of family planning, pregnancy and early parenthood in females with CF.
   4. To describe the impact of diabetes (pre-existing and gestational) on obstetric, neonatal and CF related outcomes.
   5. To record sweat chloride results during pregnancy and/or lactation among females with CF in relation to CFTR modulator therapy.
2. **Sub-studies ‘Mini’ and ‘Midi’**
   1. To collate clinically obtained serum liver enzymes levels and to record the frequency of congenital abnormalities (including ophthalmic cataract screening), in children born to a parent with CF (females or males with CF).
   2. To document cases of ‘missed’ CF-diagnoses due to false negative immunoreactive trypsinogen (IRT) results in children of females with CF in relation to transplacental and/or lactational exposure to CFTR modulators.
   3. To record lung function using lung clearance index (LCI) for young children (aged three-to-six years) born to a parent with CF.

## Exploratory Objectives

1. **Sub-study ‘Mama’**
   1. To provide biological samples to facilitate validation of a measurable assay for the individual components of CFTR modulators in maternal blood, and breastmilk.
   2. To record maternal serum and urine hormonal and micro-nutrient changes through pregnancy.
   3. To review lower respiratory tract microbiology in relation to pulmonary status (e.g. pulmonary exacerbation frequency and haemoptysis) among females with CF during pregnancy and early parenthood (up to 24 months).
   4. To identify changes in maternal bronchial artery size during pregnancy with antenatal radiological imaging (MRI) and explore rates of haemoptysis in pregnant and post-partum females with CF.
   5. To document fetal radiological findings in relation to embryological ophthalmic and pulmonary development.
2. **Sub-studies ‘Mini’ and ‘Midi’**
   1. To record blood pressure and cranial ultrasound measurements in children born to a parent with CF.
   2. To record routine neonatal health outcomes, offspring growth and developmental milestones in children born to a parent with CF.
   3. To record lung MRI results in young children (aged three-to-six years) born to a parent with CF.
   4. To provide biological samples to facilitate validation of a measurable assay for the individual components of CFTRm in the blood of babies exposed to CFTRm in utero and/or via lactation.

# Study design

## Overall design

This is a non-commercial, prospective, observational, mixed-methods study comprising three linked sub-studies, entitled **MATRIARCH_CF:** **‘Mama’, ‘Mini’, and ‘Midi’.**

A single, over-arching study protocol is warranted due to a continuation of participants, themes and data-sharing pregnant subjects (‘Mama’) and subsequent in utero environment in their offspring (‘Mini’ and ‘Midi’).

As an observational study, all the assessments described below will be optional, and participants will not be excluded from the study if they wish to decline specific investigations.

***Sub-study 1 – ‘Mama’ (pre-conception, pregnancy and parenthood)***

‘Mama’ is a sub-study of pre-conception, pregnancy and parenthood in adult females with CF. This is a prospective, mixed-methods, observational cohort study, collecting data generated in a clinical setting.

Participants will be recruited from the Royal Brompton Hospital (RBH) CF Reproductive and Maternal Health Service, up to 12 months prior to their having confirmed a planned date for actively trying to conceive, with follow-up until two years post-partum.

There will be up to a maximum of eight in-person study visits. These will occur:

- once up to 12 months pre-conception,
- once per trimester of pregnancy (X3), and
- at defined intervals post-partum.

All in-person visits will involve blood tests, lower respiratory tract samples, urine samples, lung function, health and quality of life questionnaires, in addition to taking biological samples for CFTRm assay (blood and breastmilk) and sweat chloride measurements.

The pre-conception, third trimester and 12-month post-partum in-person study visits will include radiological imaging which involves a paired synchronous lung CT and MRI when not pregnant or breastfeeding (or only MRI if visit occurs during pregnancy/lactation). In the third trimester this will also encompass a fetal MRI.

Standardised oral glucose tolerance tests will occur in the second and third trimester visits if clinically indicated (standard of care).

Semi-structured video interviews will be recorded for thematic analysis and will occur:

- once during pre-conception
- once ante-partum, and
- once post-partum.

***Sub-study 2 –’Mini’ (Offspring 0 - 24 months)***

The ‘Mini’ sub-study is a prospective, observational cohort study of children who have at least one biological parent with a diagnosis of CF. It is expected that many, but not all, of these infants will be those born to females participating in the ‘Mama’ sub-study. Any person with CF who is identified as having recently become or is due to become a parent through routine clinical visits in the RBH Adult CF Centre will also be eligible to enrol their offspring, up to 12 months of age.

Study visits for offspring exposed to CFTRm will follow the local clinical SOP (attached as a separate document) and will coincide with maternal visits in order to reduce study-burden. Tests proposed which will be additional to current clinical SOP are highlighted within this document (see table 2, section 9.4.1). All visits for those offspring *not* exposed to CFTRm, are solely for research purposes.

There will be a maximum of four in-person study visits for offspring participants within the first two years of life. The study visit review will be conducted by a paediatrician and dependent on CFTRm exposure status, will include:

- review of birth details,
- medical history (including ophthalmoscopy screening result),
- clinical laboratory tests (including liver function tests, sweat chloride, and faecal elastase),
- and physical examination.

Further investigations, not currently within our standards of practice, will include the addition of:

- Cranial ultrasound at the first visit,
- Serum CFTRm-assay levels,
- Serum samples for storage for further explorative testing if new research highlights further areas of interest.

***Sub-study 3 –’Midi’ (Offspring 3 – 6-year-olds)***

The ‘Midi’ sub-study is a cross-sectional, cohort sub-study of children aged three-to-six years who have at least one biological parent with a diagnosis of CF. Participants from ‘Mini’ will be eligible to progress into the ‘Midi’ protocol once the appropriate age has been reached. Participants will be enrolled via their parents who will be people with CF identified as under the care of the Royal Brompton Hospital Adult CF Service.

Participants who have been both exposed, and not exposed, to CFTRm will be invited to undergo the same investigations. The investigations are not invasive.

All participants aged three-to-six years will have a visit including the following, conducted by a paediatrician.

- review of birth details,
- medical history,
- neurodevelopmental milestone assessments,
- a multiple breath wash-out test to calculate lung clearance index (LCI),
- a sweat chloride test,
- physical examination,
- oxygen enhanced MRI (only performed in participants aged over five; those enrolled under the age of five will have a second visit once above five years of age as shown in section 6.2)

## Schematic of study design

Video recorded interview

Video recorded interview

Video recorded interview

MAMA

MIDI

MINI

# Eligibility criteria

## Inclusion criteria

***Inclusion criteria – ‘Mama’ sub-study:***

- Written informed consent obtained from participant.
- Under the care of Royal Brompton Hospital CF Reproductive and Maternal Health Service
- Age 16 years or above at time of recruitment.
- Confirmed diagnosis of CF.
- Planning a pregnancy or pregnant at time of recruitment.
- Ability to adhere to the required visits and investigations.

***Inclusion criteria – ‘Mini’ sub-study:***

- Written informed consent obtained from participant’s legal guardian.
- Infants who have a biological parent with a confirmed diagnosis of CF under the care of Royal Brompton Hospital Adult CF Service.
- Less than 12 months of age at first visit.
- Ability to adhere to the required visits and investigations.

***Inclusion criteria – ‘Midi’ sub-study:***

- Written informed consent obtained from participant’s legal guardian.
- Children who have a biological parent with a confirmed diagnosis of CF who is under the care of Royal Brompton Hospital Adult CF Service.
- Age three to six years at time of visit.
- Ability to adhere to the required visits and investigations.

## Exclusion criteria

***Exclusion criteria – ‘Mama’ sub-study:***

- Any significant health condition which would cause inability to comply with protocol based on investigator discretion.
- History of lung transplantation

***Exclusion criteria – ‘Mini’ sub-study:***

- Legal guardians’ inability to provide consent to participate in the study.
- Mother of infant has significant comorbidities unrelated to CF which could affect infant outcomes based on investigator discretion.
- A significant comorbidity in the infant unrelated to CFTR modulator exposure which could affect their outcomes, based on investigator discretion.

***Exclusion criteria – ‘Midi’ sub-study:***

- Legal guardians’ inability to provide consent to participate in the study.
- A significant health condition which is known to affect lung function or imaging based on investigator discretion.

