## Endpoints

### Primary endpoints

As an observational study, a combination of multiple endpoints will be monitored to identify areas of interest that may warrant and benefit from future investigation in larger studies.

Below are the endpoints which will be explored based on the currently available literature and research in the field.

*‘Mama’ sub-study*

1. Change in percent predicted FEV_1_ (ppFEV_1_) from pre-conception/baseline to end of pregnancy, and at 12- and 24-months post-partum.
2. Incidence of CF-related pulmonary complications during pregnancy.
3. Incidence of premature delivery (defined as birth <37 weeks gestation).

*Combined ‘Mini’ and ‘Midi’ sub-study*

1. The number of participants with:
2. Liver dysfunction (ALT/AST/GGT/bilirubin above upper limit of normal). This is prospectively obtained in the ‘Mini’ sub-study, and retrospectively reviewed from medical records in the ‘Midi’ sub-study.
3. Presence of congenital abnormalities including cataracts (based on medical history and examination)
4. The number of participants with normal IRT subsequently diagnosed with CF (based on a combination of CF genetic tests, sweat chloride, and faecal elastase where appropriate)
5. The number of participants with an abnormal lung clearance index (LCI) (‘Midi’ only)

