5. Number of participants with raised intracranial pressure diagnosed on cranial ultrasound (‘Mini’ only)
6. Validation of a CFTRm assay in serum (‘Mini’ only)
7. Abnormal lung branching on lung MRI. (‘Midi’ only)

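### The Midi exclusion for known lung conditions is not limited to unrelated causes, so some children with the outcomes Midi counts can be refused entry

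*Protocol*

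**What the plan says.** Section 7.2 of the protocol, repeated in the synopsis, excludes from Midi a child with "A significant health condition which is known to affect lung function or imaging based on investigator discretion". It makes no exception for CF in the child or for a condition that might result from modulator exposure.

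The infant criterion for Mini, in the same section, is narrower: "A significant comorbidity in the infant unrelated to CFTR modulator exposure which could affect their outcomes, based on investigator discretion".

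Three Midi outcomes are close to what the Midi criterion excludes:

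- Section 15.2.1 (primary, Mini and Midi combined): "The number of participants with normal IRT subsequently diagnosed with CF".
- Section 15.2.1 (primary, Midi only): the count of children with an abnormal LCI.
- Section 15.2.2 (exploratory, Midi only): "Abnormal lung branching on lung MRI".

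Section 4.2.1 explains the interest in branching. In a mouse lung explant model, the elexacaftor-tezacaftor-ivacaftor combination "adversely affected lung branching and led to the formation of abnormal bronchial terminal dilatations". The same section adds that this has not been reproduced in living animals or in humans.

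**The concern.** Whether a child may enter depends partly on what is already known about the outcomes to be counted. A child found to have CF after a reassuring screen is the event that the missed-CF endpoint is meant to record, yet CF can readily be read as a significant condition that affects the lungs. The same holds for known lung disease that could stem from exposure in utero, and for lung disease after preterm birth. Section 4.2.2 describes preterm birth as more frequent in CF pregnancies.

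Sections 4.1 and 4.3.1 say that the data should support guidance on following up these children. A count that is too low because known cases were not enrolled would be falsely reassuring. No later analysis can correct this, because a child who is not enrolled supplies no data.

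**Working it through.** **1. The plan's own figure.** Section 15.3.2 expects about 20 Midi children: about 30 existing children × 1/3 = 10, plus 15 per year × 2 years × 1/3 = 10. The total of 20 reproduces. Section 15.3.1 sets no sample size or power, so there is no power calculation to check.

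**2. Who can be lost.** Eligibility is reviewed by call before the first visit and again at that visit (section 9.4.1), so before the study's own LCI and MRI results exist.

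| Child | Can the criterion remove the child? |
|---|---|
| Abnormal LCI or branching, nothing known beforehand | No; enters and is counted |
| CF first found by the Midi sweat test | No; counted |
| CF diagnosed while in Mini | May be refused Midi, but already in the combined missed-CF count |
| CF diagnosed after normal IRT, never in Mini, before the Midi visit | Yes, at discretion; then absent from the missed-CF count |
| Known significant lung disease, possibly related to exposure or preterm birth | Yes, at discretion; then absent from the LCI and MRI counts |

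The fourth row is the clearest loss. Mini takes only infants under 12 months at first visit (section 7.1), so for the roughly 30 existing children aged three to six, Midi is the only way in. The Midi baseline already collects the IRT result and, for exposed children, any CFTR genetics (Table 3 and section 9.4.2). The information needed to count such a child would therefore be available.

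**3. Size.** One child in 20 is 1/20 = 5 percentage points of a Midi proportion. This applies to a child who would have enrolled. At one-third uptake, an ineligible child in the pool costs on average one-third of a participant. For the combined missed-CF count the share is smaller: with 25 to 35 Mini children and 20 Midi children, and none in both, one child is 1/55 to 1/45, or 1.8 to 2.2 points.

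For illustration, let p be the true share of pool children with an abnormality, and k the share of those cases already known and refused. Then

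observed share = p(1 − k) / (1 − pk), and P(no case in 20) = (1 − observed share)^20.

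The protocol gives neither p nor k, so both are assumptions. Enrolment is held at 20. Each cell shows the expected cases in 20 and the chance of seeing none.

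| p | k = 0 | k = 25% | k = 50% | k = 100% |
|---|---|---|---|---|
| 5% | 1.00; 35.8% | 0.76; 46.1% | 0.51; 59.5% | 0; 100% |
| 10% | 2.00; 12.2% | 1.54; 20.2% | 1.05; 33.9% | 0; 100% |
| 20% | 4.00; 1.2% | 3.16; 3.2% | 2.22; 9.5% | 0; 100% |

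Any k above zero lowers the count. The count is forced to zero only when every case is already known and refused. Even without selection, 0 of 20 has an exact one-sided 95% upper limit of 1 − 0.05^(1/20) = 13.9%.

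**The case against.** The criterion is modest as written. It needs a condition that is significant and known to matter, and it leaves the decision to the investigator. A reader might infer that sites must turn away every affected child and that the counts are driven to zero. The text does not support this: it permits refusal and does not require it. LCI was chosen because it detects peripheral airway change (section 9.4.11), so unrecognised abnormality will still be found. A child diagnosed in Mini is also not lost from the combined count.

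A reader might also infer that the criterion hides an effect of exposure. That is not shown. It applies to exposed and non-exposed children alike, and the direction of any bias in the section 15.4.2 comparison depends on who is refused in each group. The branching signal comes from a non-human in vitro model, and the protocol reports no child with a developmental lung abnormality caused by exposure.

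Excluding clearly unrelated lung disease is also legitimate. With about 20 children, one such case would move a proportion upwards by the same 5 points. Section 15.4.1 promises patient flow in the final report, although not reasons for exclusion by exposure group.

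All of this stands, and it limits the point. It does not explain why Midi lacks the limit that Mini has, and it does not recover a child diagnosed with CF before the visit who never entered Mini.

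**Conclusion.** The point holds in a limited form. The fault is the missing limit on cause, not the existence of an exclusion. As worded, the criterion allows partial selection on the outcome. It can lower the Midi counts of missed CF (most clearly for children never in Mini and diagnosed before the visit), abnormal LCI and abnormal lung branching.

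Only the downward direction of the counts follows from the documents. The amount depends on how many cases are already known and how investigators use their discretion, and the protocol informs neither. The table above is therefore an illustration and not an estimate. The effect on the comparison of exposed with non-exposed children could go either way.

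The study is descriptive pilot work meant to guide larger studies (sections 15.2.1 and 15.3.1). The wording should be fixed, but it does not undermine the study as a whole.

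**What to change.** In section 7.2 and the synopsis, limit the Midi criterion to significant conditions clearly unrelated to the child's CF status, parental CF or CFTRm exposure. In addition:

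- Let a child who cannot do LCI or MRI omit that test only. Section 6.1 already makes every assessment optional.
- Record any pre-existing respiratory diagnosis and its date.
- Include children with a normal IRT and an earlier diagnosis of CF in the missed-CF count.
- Report the number of children excluded on this ground, with reasons, by exposure group.
- Add a sensitivity analysis of LCI and MRI that leaves out children with a pre-existing lung diagnosis.

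Deleting the criterion altogether is not needed. The cost is a short amendment, an added case report form item for the diagnosis and its date, and a record of exclusions. The downside is a slightly more heterogeneous LCI and MRI sample, which the sensitivity analysis addresses.
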